### Participants

#### *Sample size*

In similar population-based studies which correlate the results of actigraphy against other measures, i.e. polysomnography and/or sleep diaries, the number of participants recruited varies, ranging from 30 to 450 participants [37-39]. To our knowledge, there is no published research relating to community pharmacy-based interventions utilising actigraphy in sleep health management, therefore no standard reference could be used to determine sample size required for this study. In this study, sample size calculation is based on differences in sleep parameters (sleep onset latency (SOL) and total sleep time (TST)) between actigraphy and sleep diaries [40,41]. Using Power and Sample Size Calculation software version 3.0 2009 (Vanderbilt University), to demonstrate a 20% difference in those sleep parameters between actigraphy versus sleep diary, with 80% power sample and a *p*-value of 0.05, 25 participants are required per study group. To allow for potential dropouts (approximately 10% over 2 weeks), a minimum of 55 participants will be recruited.

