## Methods and design

### Study design

This is a community-based intervention, prospective, controlled trial, with one intervention group and one control group (Figure 1).

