Follow-up after one week from baseline will be conducted in the ICG only (Table 2). Assessment (pre) of sleep parameters will be obtained from the actigraph and sleep diary for these measures: (i) Sleep efficiency percentage (SE%), (ii) Total sleep time (TST) per 24-hour period (hours/day), (iii) Number of nocturnal awakenings (NWAK), and (iv) Sleep onset latency (SOL).

Follow-up at week 2 will be conducted to complete the study in both groups (Table 2). Assessment (post) of sleep parameters will be obtained from the actigraph and sleep diary, as in previous follow-up. Participants will also complete the ‘End of Study’ questionnaires, comprise of:

• HRQOL assessment using validated WHO-Five Well Being Index (version 1998).

• Sleep health assessment (consist of ESS, ISI, MAPI and IRLSSG), adapted from POTASH [24].

• A close-out survey, consisting of: (i) questionnaire on sleep-related lifestyle and behaviour changes since completing the study, (ii) self-opinion of sleep health after the study, and (iii) willingness and ability to pay if such program is offered as a service by community pharmacy.

Upon completion of the study, pharmacists and pharmacy staff will complete a self-administered questionnaire on the feasibility of the study, and opinions on the management of sleep disorders after participating in the study (Table 2).

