#### *Study outcomes*

The primary outcomes (Table 2) of the study will be evaluated based on these three objectives:

1. To evaluate a community pharmacy-based ‘model of care’ to improve the management of sleep disorders in the community, by comparing:

a. Changes in HRQOL mean scores between and within the intervention care group (ICG) and usual care group (UCG) at baseline and week 2.

b. Changes in sleep scale mean scores – ESS, ISI, MAPI and IRLSSG, between and within the intervention care group (ICG) and usual care group (UCG) at baseline and week 2.

c. Changes in sleep parameter mean scores – sleep efficiency percentage (SE%), total sleep time (TST), number of nocturnal awakenings (NWAK) and sleep onset latency (SOL), between pre– and post–actigraphy sleep report data in the intervention care group (ICG).

2. To evaluate the role of actigraph as an objective sleep assessment instrument to monitor certain sleep disorders, by comparing:

a. Changes in sleep parameter mean scores –total sleep time (TST), number of nocturnal awakenings (NWAK) and sleep onset latency (SOL), between actigraphy and sleep diary at week 1 and week 2 in the intervention care group (ICG).

3. To evaluate the extended role of community pharmacists in managing sleep disorders in the community, by evaluating:

a. Participants’ opinions of sleep health at the end of the study.

b. Willingness and the amount able to pay if such programme is provided as a service in the community pharmacy.

Secondary outcomes (Table 2) to be evaluated are:

1. Participants’ opinions of the community pharmacy and opinions on the use of community pharmacy to seek help for sleep-related disorders.

2. Comparison between groups in sleep-related lifestyle and behaviours at week 2 follow-up.

3. Pharmacist and pharmacy staff opinions regarding the feasibility of the study and the management of sleep disorders in the community pharmacy after participating in the study.

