### Data analysis

Data will be collected from the sleep report generated from the Sleep Consultant™ software, sleep diary, and questionnaires (initial and end of study). Sleep parameters measurement, i.e. sleep efficiency percentage (SE%), total sleep time (TST), sleep onset latency (SOL) and number of nocturnal awakenings (NWAK) of a single participant through either the sleep diary or actigraphy will be averaged from all the data recorded during the 2-week period (recorded as ‘pre’ (week 1) and ‘post’ (week 2) mean scores). There will be no discrimination between weekdays and weekend data. Sleep scale scores to assess sleep health using ESS, ISI, MAPI and IRLSSG survey recorded at baseline and week 2 will be averaged to mean scores for analysis.

Data will be analysed using SPSS 20.0 for windows [53]. This study will consider alpha level of 0.05 for all statistical tests. Using descriptive, paired *t*-test and independent *t*-test – demographic characteristics and sleep scale scores between and within groups will be compared. In the ICG, pairwise differences of sleep parameters mean scores between actigraphy and sleep diary will be calculated using independent *t*-test, and will be used paired-*t*-test in comparing within group, for pre– and post–mean scores (for normally distributed data). To determine correlation between two variables, Pearson’s correlation will be applied. Likert-type questions will be analysed as descriptive analysis.

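### The 25 per group at 80% power is sized on an actigraphy-versus-diary contrast found only in the ICG, so it gives no basis for the UCG size and establishes no power for the ICG-versus-UCG primary outcomes

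*Protocol article*

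**What the plan says.** All references are to the protocol article. Under Sample size, the "sample size calculation is based on differences in sleep parameters (sleep onset latency (SOL) and total sleep time (TST)) between actigraphy and sleep diaries". The target is "to demonstrate a 20% difference in those sleep parameters between actigraphy versus sleep diary, with 80% power sample" at a p-value of 0.05, and the result is that "25 participants are required per study group". The total follows: "To allow for potential dropouts (approximately 10% over 2 weeks), a minimum of 55 participants will be recruited". The same section says that no comparable pharmacy study was available as a reference for sizing.

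Under Study design, the trial is described "with one intervention group and one control group". In Table 2, SE%, TST, NWAK, SOL and the other diary items are listed for the ICG alone. Under Study measurements, "Follow-up after one week from baseline will be conducted in the ICG only". The control-participants section has the UCG complete questionnaires at baseline and again after two weeks by email or mail.

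Under Study outcomes, objective 1a is "Changes in HRQOL mean scores between and within the intervention care group (ICG) and usual care group (UCG) at baseline and week 2". Objective 1b does the same for ESS, ISI, MAPI and IRLSSG. Objective 2a compares actigraphy with the diary within the ICG. All three are primary.

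**The concern.** The two things compared in the calculation are two instruments used by the same people. The two groups in the trial are two sets of people, and only one set uses either instrument. By attaching the result to each study group and doubling it, the section carries a within-ICG calculation over to a two-arm comparison for which it was not made.

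The outcomes left without a sizing basis are the ones that answer the first research aim, the effectiveness of the intervention against usual care. A reader who meets 80% power beside a per-group number will probably take it to cover that comparison. A null ICG-versus-UCG result could then be read as evidence of no effect, although no power was computed for it.

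**Working it through.** **Where each quantity lives**

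| Item | ICG | UCG | In the sample-size calculation? |
|---|---|---|---|
| SOL and TST, actigraphy vs diary (objective 2a) | yes | no | yes |
| WHO-5 (objective 1a) | yes | yes | no |
| ESS, ISI, MAPI, IRLSSG (objective 1b) | yes | yes | no |

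The calculation and the between-arm outcomes do not overlap.

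**Inputs.** n = 25, power 80% and a 20% difference come from Sample size. Alpha comes from Sample size and Data analysis ("This study will consider alpha level of 0.05 for all statistical tests"). Sidedness is not given, so two-sided is assumed.

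**1. The plan's own 25.** It cannot be reproduced directly, because the article gives no mean or SD. Solving backwards, with (1.960 + 0.842)² = 7.849:

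- Two-sample: d = √(2 × 7.849 / 25) = 0.79 by the normal approximation, 0.81 by the noncentral t. A 20% difference then implies an SD of 0.20 / 0.809 = 0.247, about 25% of the mean.
- Paired: d = √(7.849 / 25) = 0.56 by the normal approximation, 0.58 by the noncentral t. The SD of the differences is then 0.20 / 0.584 = 0.342, about 34% of the mean.

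Both are coherent sources for 25, and in both the 80% belongs to the device-versus-diary contrast. Because the same people supply both measurements, the paired reading suits the data. Data analysis, however, names an independent t-test for this comparison.

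**2. What 25 per arm gives for ICG versus UCG.** The article states no effect for these outcomes, so the effects below are assumed. Power is by the t distribution and the required n by the normal approximation, with participants treated as independent.

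| Assumed difference (SD) | Power, 25 per arm | n per arm for 80% |
|---|---|---|
| 0.2 | 11% | 393 |
| 0.3 | 18% | 175 |
| 0.5 | 41% | 63 |
| 0.6 | 55% | 44 |
| 0.8 | 79% | 25 |

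Power of 80% is reached at 0.81 SD.

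**3. Direction of clustering.** Participants take the group of the pharmacy they attend, and there are four to five pharmacies. With 50 completers, the mean cluster size is m = 50/4 = 12.5 or 50/5 = 10. The design effect is 1 + (m − 1) × ICC. For an assumed ICC of 0.01 to 0.05, it runs from 1 + 9 × 0.01 = 1.09 to 1 + 11.5 × 0.05 = 1.575. The detectable difference becomes 0.809 × √1.09 = 0.84 to 0.809 × √1.575 = 1.01 SD, before any allowance for the small number of pharmacies. The ICC is not in the article, so this shows direction only.

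**4. Dropout.** 2 × 25 = 50, and 50 × 1.10 = 55, which matches the stated figure. To retain 50 after 10% loss requires 50 / 0.90 = 55.6, so 56. Per arm, 25 / 0.90 = 27.8, so 28. Check: 55 × 0.90 = 49.5; 27 × 0.90 = 24.3; 28 × 0.90 = 25.2. At 24.75 per arm, power at 0.81 SD is 79.6% against 80.0%.

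**The case against.** The section is open about its basis. It names the actigraphy-diary contrast, admits that no reference study was available, and nowhere says that WHO-5 or the sleep scales have 80% power. Objective 2a is itself a primary outcome, so sizing on it is legitimate. This stands: the calculation serves one real primary objective. It does not rescue the application of the result to each study group, because the UCG contributes nothing to objective 2a.

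A reader might infer that the trial lacks power for ICG versus UCG. The article does not support that. It gives no between-group effect, and 25 per arm would reach 80% for a difference of about 0.81 SD if participants were independent. What can be said is that power was not established.

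A reader might also infer that one n for both SOL and TST forces both to share the same relative SD, or that the absent SDs are an error. Neither follows. The 25 may be the larger of two requirements, and a journal article may leave the SDs to the full protocol.

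Finally, the dropout slip might look like a sizing error in its own right. It amounts to one participant and about 0.4 percentage points of power, and the section says approximately 10% and a minimum of 55. It is a side remark.

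**Conclusion.** The point holds in this form: the 25 per group and its 80% power support the ICG size for objective 2a. They provide no basis for the UCG size and establish no power for objectives 1a and 1b. The mismatch follows from the article's own text and rests on no assumed figure.

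Its size does rest on assumptions. The detectable difference of 0.81 SD assumes two-sided alpha 0.05, 25 completers per arm and independent participants. The 41% power at 0.5 SD is an illustration for an assumed effect. Clustering by pharmacy moves the detectable difference upwards by an amount that the article does not allow one to fix.

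**What to change.** Rewrite the Sample size section along these lines:

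- Tie the 80% power to objective 2a in the ICG. If the comparison is analysed as paired, 25 participants detect about 0.58 SD of the differences. Reconcile this with the independent t-test named under Data analysis.
- State that no power was calculated for the ICG-versus-UCG primary outcomes. Report the difference detectable with 25 completers per arm: about 0.81 SD at 80% power and two-sided alpha 0.05 for independent participants, and larger once clustering by pharmacy is allowed for.
- Give recruitment per arm, since accrual follows the pharmacies. 28 per arm (56) retains 25 each after 10% dropout. Alternatively, keep 55 and say that it is expected to leave about 49 to 50 in total.

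The cost is one reworded paragraph and at most one more participant. The price is presentational: the stated power will look less favourable for the effectiveness aim.

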Currently, in managing sleep-related disorders, community pharmacists depend on self-report from patients or on sleep diaries, if indicated. Monitoring sleep disorders is difficult without appropriate tools, education or standard measures. Determining the actual sleep problem and planning meaningful strategies can therefore be complicated without objective measures. To date, in our knowledge, most studies involving sleep disorders in community pharmacies focused on screening tools [24-26] with very few studies incorporating patient follow-up and monitoring by community pharmacists [27].

This study will use a step-wise approach designed to tackle ‘poor sleep’ in all individuals with disturbed sleep, with referral procedures in place if the problem is not resolved. We will investigate the potential extended role of the pharmacists and the development of an intervention to monitor individuals with poor sleep using a convenient and portable measuring device as an objective measure to gain feedback on sleep. A wrist-actigraph (SBV2 Readiband™) allows pharmacy staff to follow those undergoing treatment by measuring the quality and quantity of sleep, and to better characterise their sleep. While monitoring treatment is difficult if self-reporting is poor, the use of actigraphy can overcomes this challenge by providing objective, patient friendly and graphical feedback that confirms certain sleep parameters and validates the self-reported feedback. An individual actigraphy report can be used as the focus reference in patients’ consultations regarding sleep.

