### Research aims

The purpose of this study is to develop an intervention to improve the management of sleep disorders in the community. The aims are: (1) to evaluate the effectiveness of a community pharmacy-based intervention in managing sleep disorders, (2) to evaluate the role of actigraph as an objective measure in monitoring certain sleep disorders and (3) to evaluate the extended role of community pharmacists in managing sleep disorders.

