**Follow-up 1** The participants will receive sleep advice and possible solutions focusing on behavioural strategies such as sleep hygiene, change of lifestyle, daily alcohol and caffeinated drinks consumption and activities before going to sleep, based on data gained from both parameters. Any requests for sleep medicine (‘Pharmacist only medicine’ or ‘Pharmacy medicine’) will follow the pharmacy’s standard practice. After this session, the participants will continue to wear the actigraph plus complete the sleep diary for another seven days.

##### 

**Follow-up 2 / end of study** Participants’ first (pre) and second (post) individual sleep reports will be compared to assess any particular improvement in their sleep condition after receiving sleep advice and possible solution during the first follow-up. Participants will also complete the ‘End of Study’ questionnaires. In certain circumstances (see the ‘Protocol to refer participant to a general practitioner’ subsection), pharmacists can recommend a GP referral for further examination.

##### 

**Protocol to refer participant to a general practitioner (GP) at the end of study** In these circumstances: (1) if the sleep efficiency percentage (SE%) is below 85% at the end of study (normal SE% for adult if measure using actigraphy is 85% and above) [41,44], and (2) if analysis of the data collected appears to indicate that he/she may be at risk of having/developing sleep-related problems and has reported symptoms such as:

• choking or suffocating during sleep

• stopping breathing when sleep

• snoring during sleep

• excessive daytime sleepiness

• difficulty falling asleep at night

• having problems waking up in the morning

• falling asleep too early at night

• waking up too early at night

• fatigue and having difficulty concentrating on daily tasks

• experiencing unpleasant sensations with an urge to move their limbs

Above symptoms may be indicative of another sleep disorders, specifically OSA, narcolepsy, a circadian rhythm disorder, restless legs syndromes or a primary mood disorder.

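### Aim 2 is about monitoring, but the actigraph is sized and tested against the diary on mean level, and no stated test compares within-person change between the two instruments

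*Protocol article*

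**What the plan says.** Research aims in the protocol article gives the second aim as "to evaluate the role of actigraph as an objective measure in monitoring certain sleep disorders". The Background says that the device "allows pharmacy staff to follow those undergoing treatment by measuring the quality and quantity of sleep". Under Follow-up 2 / end of study, each participant's two "individual sleep reports will be compared to assess any particular improvement in their sleep condition". Study outcomes lists objective 2 among the primary objectives. Its item 2a speaks of changes in mean scores of TST, NWAK and SOL, set between actigraphy and diary, at weeks 1 and 2, in the intervention group.

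Under Sample size, the "sample size calculation is based on differences in sleep parameters" (SOL and TST) and aims "to demonstrate a 20% difference in those sleep parameters between actigraphy versus sleep diary", "with 80% power sample" and a p-value of 0.05. This gives 25 per group and at least 55 in all.

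Under Data analysis, each person's nightly records are averaged to a pre (week 1) and a post (week 2) mean. Then "pairwise differences of sleep parameters mean scores between actigraphy and sleep diary will be calculated" with an independent t-test. Paired t-tests are reserved for pre versus post. Pearson's correlation is planned, but the variables to be correlated are not named.

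**The concern.** The aim, the outcome wording and the use made of the reports all concern how a person's sleep moves from one week to the next. The sizing and the one named between-instrument test concern whether two averages sit at the same level. These are different properties. An instrument can be offset by a constant and still register every change. Another can reproduce each person's usual level and register no change at all.

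The pre–post paired tests do not close the gap. They ask whether the mean moved between weeks, not whether the two instruments moved together in the same people. A Pearson correlation, if taken on weekly means, would be driven mainly by differences between people. At stake is whether primary objective 2 can answer the question for which the device is in the intervention.

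**Working it through.** **1. The plan's own figure.** For two means, n per group = 2(z₀.₉₇₅ + z₀.₈₀)² (SD/Δ)². No SD is stated, so 25 cannot be reproduced forwards. Solved backwards with Δ = 20% of the mean and an SD of 25% of the mean: 2 × 7.85 × (0.25/0.20)² = 24.5, rounded up to 25. In standardised terms 25 per group corresponds to a difference of 0.81 (independent t), or 0.58 if the 25 are pairs. For other SDs (20%, 30% and 50% of the mean) n is 16, 36 and 99. The total is 50 × 1.1 = 55. On every reading the target is a level difference; no change or within-person association enters.

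**2. What the level test can and cannot see.** All inputs here are assumptions, as the documents give none: 25 people, between-person SD 1, true week 1 to week 2 change with mean m and SD 0.5, error SD 0.3 per instrument, 20,000 trials. The 'blind' device reads the week 1 level in both weeks. The 'tracker' follows each person but adds a fixed offset.

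| Device | m | Offset | Independent t flags at either week | Paired t flags at week 2 | Paired test of changes flags | r of levels, wk 1 / wk 2 | r of changes |
|---|---|---|---|---|---|---|---|
| Blind | 0 | 0 | 0% | 5% | 5% | 0.92 / 0.83 | 0.00 |
| Blind | 0.3 | 0 | 2% | 59% | 46% | 0.92 / 0.83 | 0.00 |
| Blind | 0.5 | 0 | 22% | 96% | 87% | 0.92 / 0.83 | 0.00 |
| Blind | 0.8 | 0 | 88% | 100% | 100% | 0.92 / 0.83 | 0.00 |
| Tracker | 0.3 | 0.5 | 29% | 100% | 5% | 0.92 / 0.94 | 0.59 |
| Tracker | 0.3 | 0.81 | 99% | 100% | 5% | 0.92 / 0.94 | 0.59 |

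The correlations agree with direct arithmetic. Levels in week 1: 1/(1 + 0.09) = 0.92. Blind levels in week 2: 1/√(1.09 × 1.34) = 0.83. Tracker changes: 0.25/(0.25 + 2 × 0.09) = 0.58. A correlation of levels therefore looks good for both devices; only the correlation of changes separates them whatever the mean change.

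**3. The same in minutes of TST.** Assumed: between-person SD 60, night-to-night SD 60, error SD 30, 7 nights, 25 people.
- A tracker reading 45 min high is flagged by the independent test in 91% of trials, although its nightly within-person correlation is 60²/(60² + 30²) = 0.80. With a 30 min offset it is flagged in only 14%.
- A device with the right person average that follows neither nights nor change is flagged in 0% when sleep does not change. Its weekly-mean correlation is 0.84 to 0.90, depending on the noise given to it. Its nightly and change correlations are about 0.
- At week 2, with an assumed SD of change of 30 min, that device is flagged in 20% to 22% at a mean change of 30 min and in 73% to 78% at 45 min.

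**4. What 25 people give for a change analysis.** For a correlation, n = ((1.96 + 0.84)/atanh r)² + 3. At r = 0.5 this is just over 29, so 30. It is 85 for r = 0.3, 47 for 0.4 and 20 for 0.6. Twenty-five completers thus have 80% power only for r of about 0.53 or more. The 95% CI for r = 0.5 is tanh(0.549 ± 1.96/√22) = 0.13 to 0.75. Week 1 night pairs give more: 25 × 7 = 175, less 24 for the person means, is 151, and the interval is about 0.37 to 0.61 if nights are taken as independent.

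**The case against.** Several points on the other side stand.

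- **No decision rule.** A reader might infer that a change-blind device would pass and an offset tracker would fail. The documents do not support that. They give no agreement margin or acceptance criterion, and the sizing aims to show a difference, not to treat non-significance as success.
- **Change is unspecified, not excluded.** Item 2a says changes and covers both weeks, and the unnamed Pearson correlation could be one of changes. A condensed article may leave that choice to a fuller plan. Even so, the article fixes the data unit, the test and the sizing target, and none of these is a comparison of change.
- **The blind device is not always missed.** Once the mean change is large, the week 2 level test usually flags it.
- **Better level analyses help.** It would be too strong to say that limits of agreement leave the question wholly unanswered. Under the assumptions in minutes, the SD of paired weekly differences is √(2 × 30²/7) = 16 min for the tracker and about 34 to 35 min for the blind device. The limits are 45 ± 31 min against 0 ± 67 to 69 min, which partly separates the two. They still do not estimate whether the instruments move together within a person.
- **Level matters.** The GP referral section applies an absolute actigraph threshold (SE% below 85%), and the Background wants the device to validate self-report. The level comparison should not be dismissed.

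**Conclusion.** The point holds in a limited form. The aim, outcome 2a and the use of the reports concern monitoring and change. The sample size rests on a level difference, and the only named between-instrument test is an independent t-test on weekly means. No stated test compares within-person change between the instruments.

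The planned comparison can therefore miss a device that does not follow change when the mean change is small, and can flag a good tracker whose offset is large. How often depends on SDs, offsets and changes that are assumed throughout. Nothing in the documents suggests that this actigraph is either of the two extreme devices. The gap in what objective 2 can show does not depend on the simulated figures. It is worth closing because it is cheap.

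**What to change.** In Study outcomes item 2a and Data analysis:

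1. Compare each person's week 2 minus week 1 change in TST, SOL and NWAK between actigraph and diary. Report both the paired difference and the correlation of changes, each with a 95% CI; the paired difference alone flags a blind device in only 5% of trials when the mean change is zero. Note that the week 2 diary is kept after participants have received the day 8 report.
2. Add a night-by-night within-person association from week 1: a mixed model with a person intercept, diary value on person-centred actigraph value, with a 95% CI.
3. Keep the level comparison, since level also matters to the stated use, but analyse it as paired data.

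In Sample size:

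4. State that the 25 was derived for the level difference only.

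The diary and actigraph already cover the same 14 days in the intervention group, so no visits or participants are added. The cost is entering nightly rather than averaged values and fitting one more model.
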